# Opti-Med: the effectiveness of optimised clinical medication reviews in older people with ‘geriatric giants’ in general practice; study protocol of a cluster randomised controlled trial

**DOI:** 10.1186/1471-2318-14-116

**Published:** 2014-11-18

**Keywords:** Clinical medication review, Geriatric giants, Cluster randomised controlled trial

## Abstract

**Background:**

Inappropriate drug use has been identified as one of the most important problems affecting the quality of care in older people. Inappropriate drug use may increase the risk of the occurrence of ‘geriatric giants’ such as immobility, instability, incontinence and cognitive impairment. There are indications that clinical medication reviews (CMR) can reduce inappropriate drug use. However, CMRs have not yet been implemented at a large scale in primary care. An innovative medication review program in primary care will be developed which tackles the most important obstacles for a large scale implementation of CMRs. The aim of this study is to assess whether this CMR program is (cost-) effective compared with usual general practice care for older patients with geriatric symptoms with regard to quality of life and geriatric symptoms.

**Methods:**

A cluster randomised controlled trial will be performed in 20 Dutch general practices including 500 patients. Patients of 65 years and older are eligible if they newly present with pre-specified geriatric symptoms in general practice and chronic use of at least one prescribed drug. GP practices will be stratified by practice size and randomly allocated to control (n = 10) or intervention group (n = 10). The intervention consists of CMRs which will be facilitated and prepared by an expert team consisting of a GP and a pharmacist. Primary outcome measures are patient’s quality of life and the presence of self-reported geriatric symptoms during a follow-up period of 6 months. Secondary outcomes are costs of healthcare utilisation, feasibility, number of drug related problems, medication adherence and satisfaction with medication.

**Discussion:**

This study is expected to add evidence on the (cost-) effectiveness of an optimally facilitated, prepared and structured CMR in comparison with usual care in older patients who present a geriatric symptom to their GP. The strength of this study is that it will be conducted in daily clinical practice. This improves the possibilities to implement the CMRs in the primary care setting on a large scale.

**Trial registration:**

Netherlands Trial register: NTR4264

**Electronic supplementary material:**

The online version of this article (doi:10.1186/1471-2318-14-116) contains supplementary material, which is available to authorized users.

## Background

Inappropriate drug use has been identified as one of the most important problems affecting the quality of care in older people. Appropriate drug use and prescribing in older people is difficult, because of the variability of age-related changes in the metabolism, multimorbidity and polypharmacy [1, 2]. In addition, undertreatment of especially preventive medication as well as poor treatment adherence are frequently occurring problems in older people [3]. Because of changes in pharmacokinetics and pharmacodynamics, older people are more prone to reduced effectiveness of drugs and they may be at higher risk of adverse events and other drug related problems (DRP) [4]. Several studies have shown associations between inappropriate drug use and clinical outcomes such as hospital admissions, falling, adverse drug reactions and functional decline [3, 5–8].

Inappropriate drug use may increase the risk of the occurrence and persistence of geriatric problems [3, 5, 6, 9–15]. The most common major impairments that appear in older people, also referred to as “geriatric giants” are immobility, instability, including falls and dizziness, incontinence and cognitive impairment [16]. The atypical, silent, non-specific disease presentation of a geriatric giant is a common type of symptom presentation in the older adult and associated with limitations of activities of daily living (ADL) [7]. The multi-factorial causes of geriatric giants often include DRPs which can be prescriber-related (e.g. medically non-indicated medication or inappropriate dosage), but also patient-related, e.g. ineffectiveness of drugs, adverse effects, lack of knowledge and usage of the drugs, and non-adherence [6].

There are indications that clinical medication reviews (CMR) can reduce inappropriate drug use in older people. A CMR is ‘a structured, critical examination of the patient’s medicines with the objective of reaching an agreement with the patient about treatment, optimising the impact of medicines, and minimising the number of drug related problems’ [17]. It has been shown that specific subgroups can benefit from a CMR during or immediately after hospital admissions [18, 19]. In several countries guidelines are developed for CMRs in older and polypharmacy patients [17, 20–22]. However, CMRs have not yet been implemented at a large scale because of several obstacles.

First, the evidence for the effectiveness of CMRs is not very extensive and convincing. Several studies have shown positive effects of CMRs on intermediate outcomes such as the number of DRPs, medication adherence and patient satisfaction with medication. However, these effects are heterogeneous and so far, few effects have been established on clinical outcome measures as quality of life, hospital admissions or mortality [23–26]. This lack of evidence hinders the provision of financial incentives and motivation of healthcare professionals for further implementation of CMRs.

Second, the best target group for CMRs may be unclear. At present, patients in primary care are often selected based the number of medications, the polypharmacy criteria, which is a large group and not every polypharmacy patient may need a CMR. The current study addresses the appropriateness of medication use in patients who newly present themselves with “geriatric giant” symptoms in general practice. The patients will be selected irrespective of the number of drugs used. Previous research has shown that in many of these geriatric giants, suboptimal pharmacotherapy plays an important role in the occurrence and/or persistence of the problems. Undertreatment in these patients is just as often a problem as overtreatment [27].

The third obstacle of CMR implementation is its feasibility. A CMR requires a considerable time investment for each review varying from 15 to 60 minutes for a physician and from 30 to 120 minutes for a pharmacist [28]. The current Dutch guideline for polypharmacy in older people recommends in addition to obtain the patient’s input preferably by a home visit and follows the Systematic Tool to Reduce Inappropriate Prescribing (STRIP) method, which includes at least two patient contacts [20, 29]. In addition, both lack of knowledge as well as insufficient training of both the GPs as well as the pharmacists hinder the implementation of CMRs. Finally the lack of comprehensive organisation of medical data infrastructure and exchange between professionals are hindering factors.

In this study an innovative CMR program (Opti-Med) will be developed to tackle these obstacles in a primary care setting. This Opti-Med study aims at providing scientific evidence for the effectiveness on quality of life and geriatric symptoms of an optimally facilitated, prepared and structured CMR in comparison with usual care in older patients presenting with a new geriatric giant to their GP. The feasibility of implementing the program in the daily routine of several GP practices will be evaluated.

## Methods

The Opti-Med study protocol was approved by the Medical Ethics Committee of the VU University Medical Centre Amsterdam (reference 2011/408). For the description of the design of the Opti-Med intervention, the Consolidated Standards of Reporting Trials (CONSORT) statement with extension to cluster randomised trials is followed [30].

### Study design

A cluster randomised clinical trial will be performed in 20 general practices including 500 patients (see Figure 1). Allocation of the intervention and control condition will be carried out randomly at practice level. Eligible patients will be invited to participate in the study and the medication of the patients listed in the intervention practices will be reviewed. Patients listed in the control practices will receive usual care, with no systematic attention for their medication. The effects of this intervention will be assessed after a follow-up period of 6 months. The rationale to use a cluster design at practice level is to prevent contamination of structural attention to CMR activities within the GP practice.

**Figure 1 Fig1:**
[figure not shown]
**Study design of Opti**-**Med.**

### Setting

The study will be embedded in the Academic Network of General Practices of the VU University Medical Centre (ANH-VUmc) that consists of 20 GP practices in Amsterdam, the Netherlands. Similar to almost all GPs in the Netherlands, the GPs in this network use electronic medical record systems in which all patients contact diagnoses are coded using the International Classification of Primary Care first edition (ICPC-1) [31]. All practices employ practice nurses who can assist with the implementation of the intervention, have not yet systematically implemented structured CMR and are therefore eligible for this trial.

This CMR program is tuned to the Dutch healthcare setting where patients are listed with a general practice and their GP is the first contact point for a patient with healthcare problems. Only in case of emergency or after referral by the GP, patients visit secondary care professionals. Moreover, in the Netherlands it is common to visit one main pharmacy which provides all prescription medication. As such, the pharmacist has the most accurate and complete medication data.

### Randomisation

Randomisation will be performed by a statistician blinded to characteristics of the practices using a computer generated list of random numbers. The practices are stratified by practice size (two strata), to ensure equally sized groups. Before patients are recruited, participating practices will be randomly allocated to the intervention, or control condition. Patients will be allocated to either one of the treatment conditions, based on the practice where they are listed. Blinding of patients, GPs and practice nurses to treatment allocation is not possible due to the nature of the intervention.

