### Inclusion procedure

For identifying potential participants in the practices a two-step approach will be applied. Step 1. Eligible patients will be identified retrospectively every 8 weeks on the basis of a selected set of ICPC codes (see Additional file 1), age and chronic use of at least one drug, through a predefined search strategy in the GP electronic medical records. Only patients who consulted the GP with one of these diagnoses in this time period and who did not present with this problem to the GP during the previous 12 months are eligible to participate.Step 2. Identified potential participants in step 1 will be invited to fill out the above described screening questionnaire. If needed, the patient will be offered support at home to fill out the screening questionnaire. Patients will be included in the trial if they indicate to currently have a score of five or higher on one of the VAS scales of the geriatric problems or have indicated to have one fall or more in the previous 6 months. Additionally they have to indicate that they are willing to participate in the trial by signing an informed consent form.

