#### Exclusion criteria

Patients are not eligible when they have a diagnosis of dementia in their medical record. In addition, patients with a Mini Mental State Examination (MMSE) score of 18 or less will be excluded from the trial, since this is the cut off for serious cognitive impairment [35, 36]. An MMSE interview is only carried out when patients indicated they needed help to fill out the screening questionnaire. Each 8 weeks, the GPs will receive a list of all eligible patients and they will exclude patients who received a structured CMR in the last 6 months or are according to the GP unable to participate (e.g. due to terminal illness or severe psychiatric problems).

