### Outcome measures

Measurements by means of patient questionnaires and proxy assessments will be carried out at baseline, after 3 and 6 months It is expected that some patients will develop either cognitive problems or other difficulties precluding that they fill out the questionnaires adequately during the study. Self-assessment in these patients might therefore be less reliable or become not feasible. Proxy assessment could be a substitute for self-assessment of quality of life [38]. Therefore, patients will be asked to indicate two proxies: an informal care giver and a professional care giver who will fill out a proxy assessment questionnaire of the patient’s quality of life. Data on morbidity and laboratory test results will be collected using medical records in the GP practices. Characteristics of medication, changes in medication and adherence to medication will be assessed using dispensing data from the patient’s pharmacist. All outcomes will be assessed at patient level.

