### Secondary outcome measures

The prevalence of DRPs in patients will be determined at baseline and after 6 months in both groups. The 6 month questionnaire will be similar to the screening questionnaire omitting questions that only need to be asked at the beginning of the study. An independent clinical pharmacologist and GP will assess the DRPs on the basis of the screening questionnaire and the pharmacist’s medication overview using the DOCUMENT checklist [48]. DOCUMENT stands for Drug selection, Over- or underdose prescribed, Compliance, Untreated indications, Monitoring, Education or information, Non-clinical and Toxicity or adverse reaction and has multiple subcategories.

Research suggests that greater treatment satisfaction is associated with better compliance [49]. Patient satisfaction about medication in general will be assessed by the single-item Medication Satisfaction Questionnaire (MSQ) “Overall, how satisfied or dissatisfied are you with your current medication?” with a written response assessed on a seven point Likert like scale at baseline, 3 and 6 months [50].

Medication adherence will be measured in two ways; 1. Check for at least one pharmacy delivery in the last six months for all chronically used medication and 2. Self-reported adherence as questioned in the screening and follow-up questionnaires at baseline and 6 months. Self-reported adherence is part of the developed screening questionnaire.

Costs will be measured from a societal perspective. To calculate the costs of the intervention, information will be recorded by the expert team, the GP, the pharmacist and the practice nurse in terms of time and material spent on performing the CMR and the monitoring of the patients. Healthcare costs made by the patient will be assessed from a societal perspective using an slightly adapted version of the Dutch Medical Consumption Questionnaire (*i*MTA) questionnaire on care consumption, including informal care after 3 months (t = 1) and after 6 months [51]. Information on prescribed medication will be derived from the pharmacy administration information system (PAIS). Lost productivity costs will not be included since almost all patients will be retired. Healthcare utilisation will be valued according to guidelines for economic evaluation in healthcare in the Netherlands [52].

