Quality of life is the primary outcome measure. This may not be sensitive enough to capture the changes induced by the intervention. However, we have chosen to use generic health measures as primary outcome measures because we include patients in this study that might have a variety of geriatric symptoms with a heterogeneous treatment effect. Also we think that in this population quality of life is the most important outcome.

In addition, the study is not blinded and there is a possibility of contamination between the intervention and control group. We counter possible contamination between treatments groups by using a cluster randomised controlled design. That way, caregivers cannot unintentionally apply aspects of the Opti-Med study into their usual care for patients. Patients in the control condition also fill out the screening questionnaire on actual drug use and medication related problems, this is needed for the study, but could underestimate the effectiveness of Opti-Med by increasing awareness of possible drug related problems in these control participants. Furthermore, we suppose that current activities on older people care and possible future pharmacist’s polypharmacy projects are minimally interfering with the study. This assumption about possible contamination will be checked during the process analysis.

Implementation of structured CMR and monitoring will raise the awareness about the importance of optimising medication use in general, and especially in older patients among healthcare professionals. In this study, we will evaluate a form of a structured CMR that can easily be implemented in a GP cooperation or care group. If the CMR is shown (cost-) effective and feasible it could also be extrapolated to other groups of patients in the future in whom inappropriate medication use is suspected as well. If proven cost-effective, this will support the nationwide implementation of this structured approach. The first results of the study will be expected at the end of 2015.

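### After allocation, GPs who know their arm may exclude listed patients on an open-ended ground; separately, DRPs are scored from two sources that lack coded diagnoses and laboratory results

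*Protocol article*

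**What the plan says.** **Entry to the trial.** Under Randomisation, the Protocol article sets the order: "Before patients are recruited, participating practices will be randomly allocated to the intervention, or control condition". The same section says: "Blinding of patients, GPs and practice nurses to treatment allocation is not possible due to the nature of the intervention". Under Inclusion procedure, candidates are found "through a predefined search strategy in the GP electronic medical records", using ICPC codes, age and chronic drug use. Under Exclusion criteria, the GP then acts on the result: "Each 8 weeks, the GPs will receive a list of all eligible patients and they will exclude patients". There are two grounds. One is a structured medication review in the past 6 months. The other covers patients who "are according to the GP unable to participate (e.g. due to terminal illness or severe psychiatric problems"). Patients also need a self-reported score of at least 5 on one of the geriatric-problem scales, or at least one fall in 6 months, and must sign consent. The Control condition section says that selection is the same in both arms.

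**DRP scoring.** Under Secondary outcome measures, an independent clinical pharmacologist and a GP "will assess the DRPs on the basis of the screening questionnaire" and the pharmacist's overview of the patient's drugs, using the DOCUMENT checklist. Under Outcome measures the article also says: "Data on morbidity and laboratory test results will be collected using medical records in the GP practices".

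**Acknowledged limits.** The Discussion concedes that "the study is not blinded and there is a possibility of contamination between the intervention and control group". It then deals with contamination and with control patients becoming more aware of drug problems.

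**The concern.** Randomising practices makes the arms comparable in the patients listed with them. It does not protect the step from listed patient to trial participant when someone who knows the arm controls part of that step. An intervention GP may keep a frail patient out to spare them a review, or keep in a patient thought likely to benefit; a control GP has neither reason. Arms that differ at entry for this reason are not made comparable by randomisation, and the covariates named under Statistical analyses (gender, age, education, number of drugs, multi-morbidity) do not record a GP's view of who is fit to take part.

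The DRP issue is separate and concerns what the assessors can see. If a condition is not in their file, they can hardly recognise that it was untreated at baseline or that it was treated by 6 months. The outcome may then miss the kind of correction that the review is meant to produce.

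**Working it through.** No figure in the article bears on this point, so the check sets the steps side by side.

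**1. Who decides entry, and what they know**

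| Step (section) | Who acts | Arm known? | Room for judgement |
|---|---|---|---|
| Record search (Inclusion procedure) | Predefined search | Not relevant | None in the search itself |
| Recent structured review (Exclusion criteria) | GP | Yes | Little: a matter of record |
| Unable to participate (Exclusion criteria) | GP | Yes | Open: examples only |
| Symptom score or fall (Inclusion procedure) | Patient | Not described | Threshold fixed, answer self-reported |
| Consent (Inclusion procedure) | Patient | Not described | Patient's choice |

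All five steps follow allocation. That the GP knows the arm follows from two statements under Randomisation: allocation comes before recruitment, and GPs cannot be blinded. The third row is therefore the one step where knowledge of the arm and open discretion are both established by the text.

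**2. Whether the article deals with it.** The same procedure in both arms equalises the written rule, not what the person applying it knows. The Discussion's answer to the lack of blinding is cluster randomisation. That counters contamination, but allocating whole practices beforehand is also what makes the arm known when patients are listed.

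**3. Whether a size can be given.** Suppose a share *s* of listed patients is removed in one arm only, and those removed score *d* points below those who remain. With *R* the mean of those who remain, the full-list mean is (1 − s)R + s(R − d) = R − s·d, so removal raises the arm's entry mean by s·d. The article gives neither *s* nor *d*. Under Sample size, the 7.4-point target is a difference in change over 6 months, whereas s·d is a difference in level at entry. The two cannot be divided to give a bias in the planned effect.

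**4. What DRP assessors need and what they are given**

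- *Screening questionnaire:* severity of five geriatric problems, number of falls, weight, height, pain, drugs in use including over-the-counter drugs, and drug problems as the patient sees them.
- *Pharmacist's overview:* the patient's medication.
- *Not in either, as described:* coded diagnoses and laboratory results.
- *DOCUMENT categories affected:* untreated indications (the condition must be known) and monitoring (test results must be seen).
- *Comparison within the article:* under Preparatory steps, the review team receives the patient's medical problems and laboratory results, such as renal function. The outcome assessors are not said to receive them.
- *Relevance:* undertreatment is the first step of the review (Clinical medication review by expert team), and the Background rates it as just as frequent a problem as overtreatment in these patients.
- *Availability:* morbidity and laboratory data are already extracted (Outcome measures).

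**The case against.** The strongest reply is that discretion is narrow. GPs do not nominate patients: a fixed search does. Entry needs a fixed threshold. One exclusion ground is factual, and the examples for the other, terminal illness and severe psychiatric problems, suggest a narrow intent. Both arms get the same questionnaire with the invitation. The multilevel model uses repeated measurements, so part of an entry difference would be absorbed. All of this stands, and it reduces the risk. It does not close the open ground, and arms made up of different patients can also change differently over 6 months.

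Four stronger readings are tempting, and the article does not support them.

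- *Masking is ruled out altogether.* The Randomisation statement names patients, GPs and practice nurses only. The Discussion's remark that the study is not blinded is a general limitation. Nowhere is masking of assessors called impossible or rejected.
- *DRP scoring is unmasked.* The assessors are called independent, and masking is neither stated nor denied. A condensed article may leave this to the full protocol.
- *Patients know their arm when they answer the entry questions and consent.* What they are told at invitation is not described.
- *The bias is some percentage of the 7.4-point target.* Any such figure needs assumed inputs and sets a level against a change.

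It can also be said that the article names two DRP sources without calling them the only ones. That is fair. However, these are the sources it states, and the morbidity and laboratory data are not linked to the DRP assessment. Nor can missing reporting of patient flow be inferred, since the Methods section follows CONSORT with its cluster extension and Figure 1 is not shown. Reasons for exclusion must nevertheless be recorded at the time if they are to be reported.

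**Conclusion.** Two limited weaknesses hold.

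First, GPs who know their arm can exclude listed patients after allocation on a ground that is not closed. The safeguards limit selection bias but do not remove it, and the Discussion leaves it out. This rests on reading the two Randomisation statements together: GPs know the arm when the list arrives.

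Second, the stated sources for DRP scoring do not match the checklist or the aim of the review, while the missing data are already in hand. This rests on taking the two named sources as the full basis for scoring. It affects a secondary outcome.

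Neither effect can be sized from the document. No net direction can be given for the DRP outcome either. Missing records would tend to hide corrected undertreatment; if assessors did know the arm, scoring could lean towards the intervention; and whether they do is not stated. The changes are worth making but do not put the design in question.

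**What to change.** 1. Under Exclusion criteria, replace the open-ended GP ground with a closed list of reasons. Record one reason for every listed patient removed, in both arms, and report exclusion and consent rates by arm.
2. Under Secondary outcome measures, state that the existing DRP assessors receive files stripped of arm and practice, in random order, with the morbidity and laboratory extracts already collected.

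The cost is a tick-list for GPs every 8 weeks and some file preparation. No new assessor or data source is needed, and the sample size and the intervention are unchanged. Keeping the arm from patients until after consent and baseline would go further, but it is an ethical trade-off on which the article gives no information, so it is not proposed here.
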